# mHealth to Improve Experience, Adherence to Pharmacological Treatment, and Positive Mental Health in Patients Diagnosed With Femur Fractures: Protocol for a Quasi-Experimental Study

**DOI:** 10.2196/45856

**Published:** 2023-04-28

**Keywords:** education, patient experience, medication adherence, mental health, nurse, mHealth, mobile health, protocol, prognosis, pharmacological treatment, femur fracture, femur, diagnosis, quality of care, care, psychological, efficacy, training, pathology

## Abstract

**Background:**

Considering the prognosis of femur fractures worldwide, the ageing of our society, and the problems in adherence to treatment found in these patients, it is believed that mobile health can have a positive impact on the process and quality of care.

**Objective:**

We aim to evaluate the effectiveness of a pharmacological educational nurse intervention with Myplan app with regard to knowledge, adherence to pharmacological treatment, and positive mental health of patients with femur fractures.

**Methods:**

A nonrandomized, quasi-experimental study will be carried out with a pretest-posttest control group. It will include 278 older patients diagnosed with femur fractures, with a Glasgow Coma Scale of 15 and access to mobile devices. Patients with psychological pathologies and cognitive impairment or patients treated in isolation will be excluded. Study variables are as follows: sociodemographic variables (AdHoc Form), patient experience (Patient Experience Questionnaire-15), adherence to pharmacological treatment (Morisky-Green questionnaire), and positive mental health (Positive Mental Health questionnaire). The measurements will be taken 24 hours after admission, upon discharge, and 25 days after discharge.

**Results:**

Enrollment commenced in October 2022. Data collection will be completed in April 2023.

**Conclusions:**

The results of this study will offer evidence of the effectiveness of a pharmacological educational nurse intervention by means of a free smartphone app. If its efficacy is demonstrated and the results are acceptable, it could mean an improvement in the care of patients with femur fractures, and this technology could be used to guide other training interventions in patients with other pathologies.

**Trial Registration:**

ClinicalTrials.gov NCTT05669040; https://clinicaltrials.gov/ct2/show/NCTT05669040

**International Registered Report Identifier (IRRID):**

DERR1-10.2196/45856

## Introduction

### Overview

The estimated amount of femur fractures by 2050 is 6 million worldwide. Due to the increase in life expectancy, the incidence of femur fractures in people older than 65 years is close to 4-6 cases per 1000 inhabitants per year in Spain, Catalonia, being the region with the highest incidence of femur fractures [1]. It has been shown that the population experiencing this type of fracture exhibits a high degree of complexity, causing an increase in morbidity, mortality, and subsequently, health care expenditure [2]. It is, therefore, necessary to establish an adequate health care quality, where the affectivity of the treatment and the safety of the patient are guaranteed [3].

There is evidence of the relationship between a good patient experience and both direct and indirect clinical results, which leads to better prognosis, faster discharges, and lesser use of medication [4,5]. Another important factor is the relationship between positive mental health and capacity for self-care. The more positive patients’ mental health is, the better their ability for self-care will be, and vice versa [5-7]. Another key factor, as the literature indicates, is health education for patients regarding their illness and its treatment. The more knowledge they have, the better their health and ability for self-care will be [8,9]. We usually find education studies focused on patients diagnosed with chronic diseases [10], but we rarely find studies that evaluate the effectiveness of education and information in relation to medication adherence.

When informing patients about medication, the term “10 rights” [11] regarding the safe administration of medication should also be mentioned—inform the patient about the medication that is being used, how it must be taken, what it is being used for, and what secondary effects or adverse reactions may derive from its use. The importance of this point stands out in two aspects: (1) the patient’s health education regarding all the medications they take, so they understand everything related to the care of their illness; and (2) the potential detection of errors on the patient’s part, acting as the last filter just before the administration of the drug by the nurse. This point is so important that not informing patients is considered a medication error in some studies [12].

Prescription of medication is one of the most common interventions in clinical practice [13], and it has a significant repercussion in the time used by nurses in administrating medicines, which takes up a substantial part of their workday. Cleveland Hospital applies one of the innovative strategies in administration of medicines, named the Ask3/Teach3 initiative [14]. In this strategy, the patient is informed about the medicine, but its secondary effects are also inserted into that same conversation with the patient.

Studies in medical literature describe that the introduction of educational tools related to medication in health care organizations is linked to a decrease in hospitalization, admissions into emergency rooms, and readmissions [15]. Patients nowadays have a very close relationship with technology, as has been shown in various published studies that prove the use of apps improves health management [16,17]. Mobile health (mHealth) has opened the doors to new forms of relationships between nurses and patients, providing numerous benefits for both parties with regard to accessibility and optimization of time in office and improvement of therapeutic adherence. The mass use of web-based devices by patients older than 65 years (ie, the population sector with the highest probability of requiring medical care) has had a very positive influence in this regard [18].

It is described that there is a lack of adherence due to the complexity of the treatment, its secondary effects, lack of trust in the treatment, and the relationship between health care professionals and patients [19]. The lack of adherence can lead, firstly, to a lack of treatment effectiveness, and secondly, to a potential increase in the secondary effects of the treatment, a problem that affects 50%-60% of patients with chronic diseases. It is estimated that 20%-50% of patients do not take their medication as prescribed [20]. The index of medication adherence in these patients is only 50% [21]; therefore, improving medication adherence would result in a decrease in morbidity, mortality, and expenditure in medical care [22]. Treatment adherence is also linked to patients’ emotional well-being, the mental strength with which they face the situation, and ultimately, their level of positive mental health [23,24]. It has been observed that interventions are needed to improve lack of treatment adherence [25]. No studies have been found in medical literature on the subject of pharmacological adherence and patients with femur fractures.

One of the tools developed to complement patient education is mHealth, described by the World Health Organization (WHO) in its 2015 Global Observatory for Health report (reviewed in 2016) [26] as the use of mobile devices, such as smartphones, personal digital assistants, and patient monitoring devices, in medical practice and public health.

The WHO believes that mHealth can contribute to achieving coverage of health care at a global level, making it accessible to remote populations and communities with health service deficits. This is one of the strategic lines of the government of Catalunya. At the same time, the WHO recognizes that it is not very costly to supply these areas with mobile technology infrastructures [27].

Based on this evidence, this study proposes to respond to the needs raised so far, with the development and evaluation of a pharmacological educational nurse intervention based on a smartphone app (MyPlan app) and with regard to knowledge, pharmacological treatment adherence, and positive mental health of postoperative patients with femur fractures.

### Objectives

The primary objective of this study is to evaluate the effectiveness of a pharmacological educational nurse intervention with MyPlan app in the experience of medical assistance, pharmacological treatment adherence, and positive mental health of patients with femur fractures at the Hospital Clínic de Barcelona. We also intend to compare the pre-post intervention effectiveness in the study variables 24 hours after admission, upon discharge, and 25 days after hospital discharge.

## Methods

### Study Context

This study aims to test the nurse intervention with the added support of mHealth by creating personalized medical care and a 3-stage follow-up plan to improve the patient's experience, adherence, and positive mental health.

### Scope of Study

This project estimates the application of this approach in the Institute of Traumatology and Orthopedics of the Hospital Clínic de Barcelona between October 2022 and April 2023.

### Design

This protocol describes a nonrandomized, quasi-experimental study with a pretest-posttest control group.

### Participant Selection and Recruitment

Eligible participants will be identified in the hospitalization unit through the observation of a census by the principal investigator (PI) with a nonprobabilistic sample (according to the patients’ willingness to participate).

The sample calculation will be made by taking into account the total number of patients treated in the traumatology service for a femur fracture diagnosis during 2020. Approximately 494 patients are admitted annually with a femur fracture diagnosis. GRANMO software (version 7.12; IMIM Medical Informatics Unit) will be used with a 95% CI and a maximum indeterminacy of *P*=.5, accounting for a 15% loss, for a final recommended sample of 278 subjects to ensure a sufficient sample size for the analysis of the different variables.

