### Intervention

The final app is named MyPlan. it is based on a platform developed by the nonprofit organization Trilema, with the support of Amgen laboratory. The app is user-friendly and intuitive, and it allows patients to see their updated medication plan on their mobile phones at all times in a safe and private environment (Figure 1). One of its main functions is the daily (Figure 2) and monthly (Figure 3) calendar, and it also features reminders and allows adding programmed activities (eg, medication times, check-ups, and appointments). MyPlan is also a tool that supports treatment, allowing patients to plan and validate individual medication intake (Figure 4).

To ensure that the intervention works as expected and patients are able to access the app, the PI has a private area in MyPlan (Figure 5), where every individual patient is registered with a personal username and password. The PI will also add their individual medication plans so that patients are able to view them on the app.

The nursing pharmacological education intervention will be performed by a single nurse (an employee of Hospital Clínic de Barcelona) and the PI. This intervention consists of 4 sessions (Figure 6). First, the nurse will introduce themselves to the patient as the professional who will carry out the training session. Subsequently, patients will be informed about the intervention and its objectives. They will be introduced to MyPlan app, which will be downloaded on their smartphone, and a username and password will be generated for them (30 minutes). Then, the prescribed treatment and any questions from the patient about it will be discussed and reviewed (20 minutes). Finally, the session itself will be evaluated (10 minutes), using the Morisky-Green scale, as well as the PI’s review of the patient’s use of MyPlan during the admission, making sure they have pressed “OK” at the time they were taking the medication according to the prescription.

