### Procedure

Following the inclusion and exclusion criteria defined in the study, the patient will be requested to answer the different questionnaires described in the “measurement tools” section.

The PI will download the MyPlan app for the patient and explain its function to them. The PI will also manually transcribe the treatment that has been prescribed for the patient’s hospitalization time. The medication that must be administered to the patient and the medication schedule will be added into the app. The PI will also carry out a basic training session for each medicine prescribed to the patient, including what the drugs are for and their possible adverse effects.

During hospitalization, the same procedure will be repeated every day from Monday to Friday. A minimum of 4 sessions, as described above, will be held to educate the patient and improve their knowledge in pharmacology and autonomy upon discharge. The PI will maintain an individual registry in a Microsoft Excel spreadsheet that will contain all adverse drug reactions notified in the patient’s clinical history. These data will be extracted from the information in the Systems Applications and Products in Data Processing bed chart (there is a shortcut icon for adverse drug reactions notifications), which is filled in by the medical professionals in charge of any given patient during hospitalization when applicable. As soon as the patient has been deemed fit to be discharged, the treatment prescribed for the time after discharge will be explained to them using the app (we will restrict the explanations to those pertaining to the treatment specified in the discharge report). It will be explained to them that they can use the app during the 30 days following discharge, as long as their primary care doctor does not make modifications to the treatment. For this reason, the patient’s history will be reviewed daily by the PI to make sure there have been no consultations that have resulted in a change in the medication; 25 days after discharge, the PI will contact the patient via the MyPlan app to ask them to fill out the questionnaires and remind them that the study will end 5 days later (ie, 30 days after discharge). A message will be sent to the patient via the app 30 days after discharge to thank them for participating in the study, and their access to the app will be blocked, considering that the intervention has concluded.

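### The article claims a control group, but its recruitment, procedure, data collection and analysis describe one pathway in which every enrolled patient gets the app and training, so no comparator exists as written

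*Protocol article*

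**What the plan says.** The Methods part of the Abstract and the Design section both announce a control group. Design reads: "This protocol describes a nonrandomized, quasi-experimental study with a pretest-posttest control group".

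The operational sections read differently:

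- **Participant Selection and Recruitment** gives a single stream: "Eligible participants will be identified in the hospitalization unit through the observation of a census by the principal investigator (PI) with a nonprobabilistic sample", taken "according to the patients’ willingness to participate". It sets one total of 278, with no group sizes or ratio.
- **Intervention** states: "The nursing pharmacological education intervention will be performed by a single nurse (an employee of Hospital Clínic de Barcelona) and the PI". It describes a private area of the app "where every individual patient is registered with a personal username and password". The end of that section says the questionnaires have been built into the app.
- **Procedure** starts from the eligibility criteria and the questionnaires, then continues: "The PI will download the MyPlan app for the patient and explain its function to them". Next comes: "The PI will also carry out a basic training session for each medicine prescribed to the patient". Sessions repeat on weekdays, at least four in all. The day-25 questionnaires are requested through the app.
- **Demographics and Baseline Functioning** places collection of background data in the first intervention session.
- **Data Analyses** bases its indicators on change from before to after the intervention, across the three measurement points.

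Potential Limitations and Implications concedes that the sample is not randomized. It does not say how a control group would be formed.

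**The concern.** The Objectives section asks whether the intervention is effective for patient experience, adherence and positive mental health, and the Conclusions promise evidence of effectiveness. The first measurement falls 24 hours after admission with a femur fracture and the last falls 25 days after discharge. Patient experience and positive mental health can both move over that interval as patients recover and go home, whether or not anyone trains them. A control group measured at the same points is what would separate that movement from the intervention. The label promises such a group, but the instructions do not produce one.

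A team that follows the instructions ends with an uncontrolled before-after study reported under the name of a controlled one. A team that tries to honour the label finds nothing in the article on whom to assign, what controls receive, or how to collect their data.

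**Working it through.** The question is structural, so the main check sets the sections side by side and asks what each would have to contain if a control group existed.

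| Element needed for a control group | What the article contains |
|---|---|
| A rule that assigns patients to groups | None. One recruitment stream from the ward census |
| Group sizes or ratio | None. A single total of 278 |
| A control condition | None. Only the app and training are described |
| A branch in the procedure | None. Eligibility, questionnaires, app, training, app follow-up |
| Baseline data for untrained patients | None. Background data come from the first intervention session |
| Questionnaires for patients without the app | No route described, and the day-25 request is sent through the app |
| A between-group contrast | None named. Change across phases only |

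The Design label and the Abstract that repeats it stand alone. Every operational section points to one arm.

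**Count under the text as written.** Enrolled: 278. Registered in the app and trained: 278. Controls: 278 − 278 = 0.

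**Does the sample size contain a control arm?** The stated inputs are about 494 admissions a year, 95% confidence, p = 0.5 and 15% loss. These belong to estimating one proportion in a finite population:

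- n0 = z²·p(1 − p)/d², and n = n0·N/(N − 1 + n0), with z = 1.96, p = 0.5, N = 494.
- The precision d is not stated. At an assumed d = 5%, n0 = 384.16 and n = 384.16 × 494/877.16 = 216.4, rounded up to 217. With loss, 217/0.85 = 255.3, rounded up to 256. This does not reproduce 278.
- Solving for 278 gives d = 4.61%: n0 ≈ 452, n ≈ 236, and 236.3/0.85 = 278.

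So 278 is reached by this formula only with a precision that the article does not give. For the present point, what matters is the form of the inputs. There is no effect size, power or allocation ratio, so no second group is visible here either.

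**What 278 would give if split (illustration).** Assume a 1:1 split and 15% loss: 278 × 0.85/2 = 118 per group. With two-sided 5% tests, power is 34%, 65% and 89% for 50% versus 60%, 65% and 70%. For standardized mean differences of 0.2, 0.3 and 0.4 it is 34%, 63% and 87%. These effect sizes are assumed.

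**The case against.** The best defence is condensation. A journal article may describe in detail only what the app recipient gets and leave allocation and control care to a full protocol. The sentence about registering every individual patient explains the app's private area and need not mean every study participant. The factorial ANOVA could hold a group factor that is not mentioned, and controls might come from a sequential cohort. The lack of randomization is openly disclosed.

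Part of this stands. The count of 0 controls is a reading of undifferentiated wording, and a fuller document might contain a control arm. But the defence does not explain why the general sections, and not only the description of the intervention, presuppose it: participants' background data come from an intervention session, and the indicators are defined as change around the intervention. That is a contradiction within the article, not a detail left out of it. Admitting non-randomization does not tell the reader how groups arise.

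A reader might go further and infer that willingness or PI choice sorts patients into arms, so that motivated or longer-staying patients end up with the app. The article does not support this. Willingness there refers to joining the study, and nothing says that the PI or the patient picks a group. That the PI both identifies patients and delivers the intervention is a reason to take group formation out of the PI's hands, not evidence of how groups were formed. Nor does the article say that controls would be concurrent on the same ward.

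A reader might also infer that any group imbalance would be beyond repair. That too goes too far. A stable difference already present at 24 hours would largely cancel in an analysis of change, and the 24-hour scores are available for adjustment.

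**Conclusion.** The point holds as a contradiction. The Abstract and Design claim a control group, while recruitment, intervention, procedure, baseline collection and analysis describe one treated stream. As written there is no comparator, and an intervention effect cannot be told apart from natural recovery between 24 hours after admission and 25 days after discharge. The resulting bias cannot be sized, because the article gives no expected course for untreated patients.

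This must be resolved, since the primary objective depends on the comparison. The conclusion rests on two assumptions: that the operational sections apply to all enrolled patients, as their wording says without exception, and that no unseen document overrides them. It does not rest on any claim about who would choose the arms.

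**What to change.** **If patients can still be enrolled**, revise these sections:

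- **Design, and Participant Selection and Recruitment:** form the groups by a rule outside the discretion of PI and patient. One example is calendar periods fixed in advance. Make them long enough, or separate them by a gap, to limit ward overlap; with at least four weekday sessions, one-week blocks would often be crossed. Apply the same entry criteria in both periods, including access to a mobile device.
- **Procedure:** obtain consent and the 24-hour questionnaires before the group is disclosed. State that controls receive the unit's usual medication information. Collect all three measurements in both groups by a route that does not need the intervention.
- **Demographics and Baseline Functioning:** move background data collection out of the first intervention session.
- **Data Analyses:** name a between-group comparison of change, adjusted for the 24-hour score.

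The cost is mainly wording. The rule itself needs no extra staff or patients. The small downside is some ward overlap or calendar-time difference between groups, which can be recorded. Whether 278 suffices for a two-group comparison is a separate question that the sponsor should answer with a stated effect size.

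**If enrolment is complete**, which is likely because it was due to end in April 2023 and the article is dated 28 April 2023, a prospective rule is no longer possible. State how and when any controls were formed and what they received. If there were none, delete the control-group label from the Abstract and Design, and limit the conclusions in the Abstract and the Discussion to uncontrolled before-after change. The cost is the loss of the effectiveness claim.

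### The basis given for 278 fits the estimation of one proportion in a finite population, so the claim that it suffices for the controlled comparison is unsupported

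*Protocol article*

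**What the plan says.** Under Participant Selection and Recruitment, the protocol article bases the target on the number of patients in the service: "The sample calculation will be made by taking into account the total number of patients treated in the traumatology service" in 2020, and "Approximately 494 patients are admitted annually with a femur fracture diagnosis". GRANMO is to be used "with a 95% CI and a maximum indeterminacy of" P=.5, and the result is given as "accounting for a 15% loss, for a final recommended sample of 278 subjects to ensure a sufficient sample size for the analysis". The same sentence says that this number is meant to be enough for analysing all the study variables. The paragraph calls the sample nonprobabilistic and gives no margin of error, effect size, power, standard deviation or allocation between groups.

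The Design section reads: "This protocol describes a nonrandomized, quasi-experimental study with a pretest-posttest control group". Objectives sets an effectiveness aim on patient experience, adherence and positive mental health. Data Analyses plans ANOVA across three measurement times, with differences of proportions and Cohen d as effect measures.

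**The concern.** A population total and a worst-case P of .5 are what one enters to find how many people to survey so that one percentage is known to within a set margin. Neither has a role in sizing a comparison between an intervention group and a control group. Yet the paragraph says the resulting number is sufficient for the analysis, and it is the only justification given for the size of the study.

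What is at stake is how the result will be read. If the groups do not differ clearly, a reader may rely on the stated sufficiency and take the finding as good evidence of no effect, although the basis shown does not say which differences the study could detect.

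**Working it through.** **1. Inputs.** From Participant Selection and Recruitment: N = 494, 95% confidence (z = 1.96), P = .5, loss 15%, stated total 278. The margin d is not given.

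**2. Reproducing 278.** For one proportion with finite-population correction:

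- n0 = z² × 0.25 / d²
- n = N × n0 / (N − 1 + n0)
- loss added as n/0.85 or as n × 1.15

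| d | n0 | n | n/0.85 | n × 1.15 |
|---|---|---|---|---|
| 5% | 384.1 | 216.3 | 254.5 | 248.8 |
| 4.6% | 453.9 | 236.8 | 278.6 | 272.3 |
| 4.5% | 474.3 | 242.2 | 285.0 | 278.6 |

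Rounding 216.3 up to 217 before adding loss gives 256 or 250, so a 5% margin yields about 249 to 256. The stated 278 is recovered at about 4.6% (loss by division) or 4.5% (loss by multiplication). If the margin were 5%, 278 would need a population of about 612 (division) or 650 (multiplication) instead of 494. The figure is therefore consistent with this type of calculation at a margin that the article does not print.

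**3. Does the correction suit the study?** The finite-population correction assumes a probability sample from the fixed population about which one wishes to infer. Here the sample is nonprobabilistic, the count comes from 2020, enrolment runs from October 2022 to April 2023 (Scope of Study), and the conclusions are meant to guide later care. Without the correction, a 5% margin needs 385 evaluable, or 453 with loss by division. The evaluable number behind 278 (278 × 0.85 = 236.3) would give a margin of 0.98/√236.3 = 6.4%.

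**4. What 278 gives for two groups.** Assumptions not in the article: 1:1 split, unadjusted comparison at one time point, two-sided 5%. Then 278/2 = 139 per group and 139 × 0.85 = 118 evaluable. The 50% reference is the adherence figure in the Introduction, which is given there for patients with chronic diseases.

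Power = Φ[(Δ − 1.96 × SE0)/SE1], where SE0 = √(2p̄(1 − p̄)/118) and SE1 = √((p1(1 − p1) + p2(1 − p2))/118):

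- 50% vs 60%: (0.10 − 1.96 × 0.0648)/0.0644 = −0.42, power 0.34
- 50% vs 65%: (0.15 − 1.96 × 0.0644)/0.0636 = 0.38, power 0.65
- 50% vs 68%: (0.18 − 1.96 × 0.0640)/0.0630 = 0.87, power 0.81
- 50% vs 70%: power 0.89

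The standardised mean difference detectable with 80% power is (1.96 + 0.84) × √(2/118) = 0.36. The 95% CI half-width for a difference of proportions near 50% is 1.96 × √(2 × 0.25/118) = 0.128, or 12.8 points.

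**The case against.** Four points can be made for the plan.

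- **No arithmetic error is shown.** A reader might infer from the 5% row that 278 is miscalculated. The documents do not support that: 5% is not a stated input, and 4.5% or 4.6% reproduces 278. An unprinted margin in a condensed article is not a finding in itself. This stands.
- **The method is inferred.** Neither the GRANMO module nor a finite-population correction is named. This stands as a caveat. But a population total with P at maximum indeterminacy fits no two-group method, and nothing else is given that would.
- **The study is not without power.** A reader might infer that 278 is simply too small. The documents do not support that either. On the assumptions above, power is 0.89 for 50% vs 70% and 0.87 for a standardised difference of 0.4. The calculation fails to establish power, which is different from power being low.
- **The illustration is not the planned analysis.** Data Analyses speaks of change over phases. Within-person change in 236 people is detectable at about 2.80/√236 = 0.18 SD. For scores, baseline adjustment with an assumed correlation of 0.5 to 0.7 lowers 0.365 to 0.365 × √(1 − 0.25) = 0.32 or 0.365 × √(1 − 0.49) = 0.26. This also stands, so the figures in step 4 are a sensitivity statement. Within-person change does not, however, answer the question for which the control group exists.

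None of this rescues the sufficiency claim. A separate analysis plan could add a power statement, but it could not make a one-proportion calculation support the sentence as printed.

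**Conclusion.** The concern holds as a fault in justification. The stated inputs fit the estimation of one proportion in a finite population, they establish no power or precision for intervention versus control, and the correction does not suit a nonprobabilistic sample used to infer to future patients. The statement that 278 is sufficient for the different variables is therefore unsupported.

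On size: under the illustrative assumptions the study detects large differences (about 18 points, or 0.36 SD) with 80% power and would often miss differences of 10 to 15 points. These figures depend on the 1:1 split, 15% loss, the 50% reference and an unadjusted comparison. Unequal groups would raise the detectable difference, and baseline adjustment of scores would lower it. Nothing in the article shows 18 points to be an expected or relevant effect.

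**What to change.** Keep 278. Delete the finite-population rationale and the claim of sufficiency. Name one primary endpoint and the between-group comparison on it. That choice is the sponsor's, since Objectives lists three outcomes together, and it should be made before outcomes are compared by group. Then state how the 278 divide between groups and what that delivers, for example:

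> The target of 278 was not derived from a power calculation. If divided equally, with 15% loss (118 evaluable per group), an unadjusted two-sided 5% test has 80% power for a difference of about 18 percentage points from 50%, or a standardised mean difference of about 0.36. The 95% CI half-width for a difference of proportions is about 12.8 points.

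The figures must be recomputed for the endpoint, split and analysis actually chosen, and presented as what the sample can detect, not as a target effect. If the original calculation is kept on record, its margin should be given.

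The cost is one paragraph. The stated sufficiency becomes less favourable, and no more patients are needed.
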